## Abstract

**Background:**

Automatic tendencies to approach drug-related cues have been linked to the development and maintainance of harmful drug-taking behavior. Recent studies have demonstrated that these automatic approach tendencies can be targeted directly by means of cognitive bias modification (CBM). Moreover, changing those approach tendencies may enhance treatment outcomes. However, training and therapy effects tend to be rather small and adherence to the training might be impaired by time-consuming multiple laboratory training sessions. Here, we present a protocol for a randomized controlled design to improve CBM training efficiency and facilitate access to the training by providing mobile-phone-based training sessions at home to current smokers motivated to quit smoking.

**Methods:**

Participants (*n* = 100) are current smokers who smoke at least six cigarettes per day for at least 6 months and are willing to quit smoking. All participants attend a brief behavioral smoking cessation intervention (TAU) and are randomly assigned either to an experimental (TAU + training) or a control group. Participants in the experimental condition are given access to a training application (app) aimed at retraining automatic approach biases for smoking cues. Participants are instructed to perform the app training outside the laboratory context on a daily basis for 14 consecutive days. Participants in the control group do not receive the training. Primary outcome measures are changes in smoking-related approach biases and reductions in daily nicotine consumption as assessed at baseline, post-training and at 6-week follow up. Secondary outcome measures include approach biases for alternative stimuli or smoking stimuli to which participants were not exposed during training, attentional and association biases, biochemical outcomes, and self-reported smoking behavior, also measured at three different time points (baseline, post-training, and follow up). After completion of the study, smokers in the control condition will receive access to the training app.

**Discussion:**

This randomized controlled trial is the first to test the effectiveness of an app-based CBM intervention as an adjunct to a brief smoking cessation intervention in smokers motivated to quit smoking. The results of this study can inform future research in the optimization and advancement of CBM treatment for addiction.

**Trial registration:**

Current Controlled Trials, ISRCTN15690771. Registered on 20 November 2018.

## Background

Tobacco smoking remains a major public health problem. Smoking is considered the largest preventable risk factor for morbidity and mortality worldwide, with smoking-related deaths estimated at over 5 million people per year [1]. In addition, smoking is strongly implicated in poorer quality of life [2] and imposes a considerably high economic burden on the healthcare system. For instance, it is estimated that smoking-related diseases are responsible for 1.5–6.8% of national health system expenditure [3].

Despite growing evidence about the hazardous effects attributed to smoking, prevalence rates are still high. In Germany, approximately 25–30% of the adult population smoke [4], mostly on a daily basis. Although many smokers want to stop smoking and quit attempts are frequent, relapse rates are upsettingly high [5, 6]. Even following effective treatment, only about one out of four smokers will achieve sustained (≥ 6 months) abstinence [7–9]. Thus, there is an urgent need for developing more effective treatment options and/or improving the efficacy of the available smoking cessation interventions.

While most common interventions for smoking cessation rely on reflective reasoning (i.e. through education on smoking-related health risks, motivational interviewing, and pro–con debates), prominent theories of drug addiction [10, 11] and recent research [12, 13] insist on the notion that more automatic, hard-to-control impulsive processes are strongly implicated in the development and maintenance of addictive behaviors. According to dual-process theories, addiction arises from an imbalance between strengthened impulsive processes at the expanse of weakened reflective processes [10, 11]. Specifically, it is proposed that drug-related cues acquire motivational properties as they predict the availability of drugs, predispose drug taking and/or are associated with rewarding drug effects [14]. Hence, as addiction progresses, information processing is biased in favor of drug-related cues, resulting in various cognitive biases. For instance, research indicates that smokers automatically allocate their attention to smoking-related cues (attentional bias [15, 16]), display implicit positive attitudes toward smoking (association bias; for a review, see [17]), and automatically approach smoking-related cues (approach bias [18, 19]). While all of these biases have been linked to craving, drug seeking and drug use, the approach bias might most strongly relate to actual drug taking, since it incorporates biased information processing with actual motor movement.

Recent research shows that it is not only possible to measure cognitive biases using computer-based tasks, but that such tasks also have merit in modifying existing cognitive biases to promote healthier behavior or abstinence from drug use [12]. In this instance, the Approach-Avoidance Task (AAT) [20] has proven particularly valuable in both measuring and modifying a drug-related approach bias [18, 21]. During the task, different pictures are consecutively presented on a computer screen and participants are instructed to ignore image content and to pull or push a joystick attached to the computer depending on a content-irrelevant feature of the task (i.e., pull all images rotated to the left and push all images rotated to the right). In addition, the AAT incorporates a zoom feature: upon a pull movement, the picture becomes bigger, whereas upon a push movement the picture shrinks, creating a visual sense of approach versus (vs) avoidance. An approach bias is inferred from faster pulling than pushing a picture (e.g., a smoking-related picture). Using the AAT, an approach bias has been associated with different substances, including alcohol [22], cannabis [23], heroin [24], and recently nicotine [18]. Furthermore, an approach bias for cigarette cues has been reported in current smokers, but not in ex-smokers or never-smokers [19]. Lately, the AAT has been adapted to a training variant by changing the contingency between picture content and arm movements, namely by presenting all drug-related pictures in push-away format and all neutral pictures in pull-closer format, thus training automatic avoidance in response to drug-related stimuli. Recently, we applied four sessions of AAT-training as an add-on to a brief smoking cessation intervention in a sample of smokers hospitalized in a psychiatric ward [21]. Compared to sham training where smoking-related pictures had to be pulled and pushed equally often, the AAT-training led to a larger reduction in nicotine consumption at 3-month follow up. In another study conducted by Baird and colleagues [25], smokers motivated to quit were assigned to four sessions of AAT-training or sham training and were asked to make a self-guided quit attempt upon completion of the final training session. Results indicated that the reduction in approach bias was related to the number of days abstinent following the quit attempt. Hence, emerging evidence suggests that cognitive bias modification (CBM) by means of the AAT-training might be a useful intervention to reduce smoking or promote abstinence, but effects tend to be small in size or are even mixed sometimes [26]. Several reasons may account for these heterogeneous findings, with adherence to the demanding training protocols and generalization of training effects among the most significant. For example, although the optimal number of training sessions is still unknown (but see [27], for a systematic investigation on the optimal number of training sessions in the context of alcohol-avoidance training), it seems that training should be administered multiple times to produce stable and long-term improvements. Thus, participants are required to keep multiple training appointments, which begs the question of whether individuals are able to maintain adherence to a daily or weekly training prescription. Indeed, preliminary evidence suggests that high dropout rates are an issue of concern in CBM studies (e.g., [21, 28, 29]). The second reason for rather small training effects concerns the ecological validity of the training tasks. For instance, training takes place in a laboratory context that participants have never before associated with craving, drug taking, or beneficial drug effects. Increasing evidence from the literature on cue exposure and from extinction learning suggest that generalization is inhibited if it takes place in only one context [30–32], leading to reduced treatment effects or increased relapse rates. Thus, CBM efficiency and effectiveness could be improved if the optimal parameters for bias modification are met, including the number and context of training sessions.

One way to improve training adherence and provide varying training contexts could be to apply them via smartphone application (app). An increasing number of people owns smartphones (i.e., 78% in Germany). Moreover, it is estimated, that 3.1 billion people will own a smartphone by the year 2021 [33]. Thus, through smartphone-delivered AAT-training, participants can perform training more often and in the exact same environment in which they otherwise smoke cigarettes, thereby facilitating generalization of training effects.

This study investigates the effectiveness of an app-based AAT-training (app-AAT) for smokers motivated to quit smoking and its effects on the malleability of the smoking-related approach bias, nicotine consumption, and smoking behavior, including cessation. It features a randomized controlled design and multi-session training by means of a newly developed app-based AAT-training during a 2-week training period. We expect that the app-AAT would reduce smoking-related approach biases as measured using the assessment version of the standard AAT [18] and reduce the number of daily smoked cigarettes over and above the control condition.

## Methods/design

### Trial design

The present study is a randomized controlled trial (RCT) comparing self-report, behavioral, and biochemical outcomes of the app-AAT training to a control condition, in which the app training is not received (Additional file 1). Prior to randomization, all smokers included in the study receive standard help for smoking cessation (cf. precise description subsequently). This study employs a 2 (training: training/control) × 3 (time: pretest/posttest/follow up: 6 weeks after baseline) mixed design. The training intervention occurs over the course of 2 weeks in which smokers are given the opportunity to complete AAT-training sessions at home.

### Outcome measures

We focus on two primary outcome measures: (1) changes in smoking-related approach biases with regard to smoking stimuli presented during training (measured in milliseconds) and (2) reductions in self-reported daily cigarette smoking (measured in number of smoked cigarettes per day). Primary time points include post-training and follow-up assessments. Secondary outcome measures are (1) changes in smoking-related approach biases with regard to untrained pictures (close generalization), (2) changes in approach biases for positive pictures, (3) changes in other cognitive biases as measured by the visual dot-probe task and the Implicit Association Task (IAT) (broad generalization), (4) self-monitored smoking behavior using a cigarette tracking app, (5) biochemically verified abstinence rates defined as point prevalence with a 7-day window prior to the assessment point, (6) expired CO, and (7) other self-reported smoking behavior.

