### Sample size

A priori power analyses were conducted using G*Power 3.1 (open-source software [34]). Previous research investigating the effectiveness of CBM training identified a small-to-moderate effect size [21, 35]. We conducted a power analysis for a 2 × 3 mixed design ANOVA to detect a small-to-moderate effect (Cohen’s *d* = 0.30, α = 0.05) for the interaction between experimental condition and time for each primary outcome and time point. Power of 0.80 and *r* = 0.5 for correlation between the repeated measures was assumed. Results indicated that 74 participants in total would be needed. Due to an expected attrition rate of approximately 25% at follow up (defined as dropout at any time point after completing the baseline assessment), we decided to include 100 participants, that is 50 per condition.

We would like to stress that we performed power calculations for primary outcomes exclusively. With regard to secondary outcome measures, we emphasize that the study is explorative, meaning that any significant findings on these outcome variables should be interpreted with caution until tested in further confirmatory RCTs.

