### Data preparation and planned analyses

Multiple imputation of missing data will be performed for intention-to-treat (ITT) analyses [54]. To analyze changes in cognitive biases, error trials will be excluded from further analyses. Median RTs will be used to minimize the influence of outliers.

To investigate whether the app training leads to changes in the primary outcome measures, two separate 2 (condition: training vs control) × 3 (time: baseline, post-training, follow up) mixed design analysis of variance (ANOVA) will be performed. Changes in smoking approach biases and self-reported daily nicotine consumption will constitute the primary dependent variables. A separate univariate test will determine if there are significant differences in smoking-related approach biases or average nicotine consumption at baseline between the app training and the control group. Due to the random assignment to the experimental or to the control group, we expect a priori group differences to be small. Nevertheless, chance baseline imbalance between treatment arms will be taken into account, when evaluating training effects. Substantive hypotheses will be tested by means of follow-up simple effects analyses. Here, we compare means in the app training and control group (posttest and follow up, respectively), while controlling for baseline approach bias and nicotine consumption levels. We apply a mixed design ANOVA as one factor (a fixed effects factor) is a between-subjects variable (here, condition) and the other (a random effects factor) is a within-subjects variable (here, time).

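### Two primary outcomes are each tested at 0.05 with no success rule, so the chance of a false primary finding is about 10%, and about 18% if visit comparisons do not require a significant interaction

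*Protocol article*

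**What the plan says.** In the protocol article, the section Outcome measures says "We focus on two primary outcome measures": approach bias for the smoking pictures used in training, in milliseconds, and self-reported cigarettes per day. It continues: "Primary time points include post-training and follow-up assessments".

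The section Sample size gives the error level as "α = 0.05) for the interaction between experimental condition and time for each primary outcome and time point". With Cohen's d = 0.30, power 0.80 and a correlation of 0.5 between repeated measures, it arrives at 74 participants, raised to 100 for 25% attrition. It then limits its caution: "With regard to secondary outcome measures, we emphasize that the study is explorative".

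The section Data preparation and planned analyses sets out one 2 × 3 mixed ANOVA per primary outcome. It adds: "Substantive hypotheses will be tested by means of follow-up simple effects analyses". These compare the groups at posttest and at follow-up, adjusted for baseline. The section mentions no multiplicity adjustment, no order of testing and no requirement that both outcomes succeed.

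**The concern.** Two outcomes at two visits give several chances of a significant primary result, each at 0.05. Only the secondary outcomes are set apart as explorative, so the primary tests are the ones a reader will treat as confirmatory. Because no success rule is given, the plan does not prevent a reaction-time effect alone, or a drop in cigarettes at one visit alone, from being reported as a positive primary finding. A training effect on a laboratory task and an effect on smoking are very different claims, so it matters which of them the trial may make and at what error rate.

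**Working it through.** **Inputs.** From the article: 2 primary outcomes, 2 primary visits, alpha 0.05, d = 0.30, r = 0.5, power 0.80, 74 evaluable, 25% attrition. Assumed: f = d/2 = 0.15, two-sided visit comparisons, and a correlation between the two outcomes of 0 to 0.5, which the article does not give.

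**1. The plan's own figure.** For the condition-by-time interaction with m = 3 time points and 2 groups:
- noncentrality λ = f² × N × m / (1 − r), with df = 2 and 2(N − 2)
- N = 74: λ = 0.0225 × 74 × 3 / 0.5 = 9.99, df = 2 and 144, power 0.806
- N = 72: power 0.795

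The smallest even N reaching 0.80 is 74, as stated. Attrition gives 74 / 0.75 = 98.7, so 99, planned as 100. The sample size therefore rests on one outcome at an unadjusted 0.05.

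**2. Two interaction tests, no true effect.** With independent outcomes, 1 − 0.95² = 9.75%. Simulation of the two ANOVAs (N = 74, 20,000 runs per setting, time correlation 0 to 0.8, outcome correlation 0 to 0.5) gave 9.4% to 10.1%.

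**3. Four baseline-adjusted visit comparisons, run whatever the interaction shows.**
- r = 0.5 implies a partial correlation between visits, given baseline, of (0.5 − 0.25) / (1 − 0.25) = 1/3
- P(at least one of two visits significant) = 0.0946
- two independent outcomes: 1 − (1 − 0.0946)² = 18.0%
- range: 17.3% to 18.5% for a between-visit correlation of 0.5 down to 0
- simulation: 17.4% to 18.2% at r = 0.5, and 16.5% to 18.4% over all settings

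**4. Visit comparisons only after a significant interaction in the same outcome.** Simulated false visit-level claims with no true effect anywhere: 5.7% to 7.7%, about 6.5% at r = 0.5. The interaction tests themselves remain at about 10%.

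**5. Success only if both outcomes have a significant interaction.** Below 1% when neither outcome responds.

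**6. Power if alpha is split evenly.** At 0.025 and N = 74, power is 0.719. Reaching 0.80 at 0.025 would need 88 evaluable, or 88 / 0.75 = 117.3, so 118 enrolled.

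**The case against.** The strongest reply is that a journal article often leaves multiplicity rules to the analysis plan, and that the 0.05 is an input to a power calculation, since the analysis section names no alpha. A mere gap would indeed be no finding. But the article goes further: it fixes 0.05 for each outcome and time point, sizes the trial on it and confines its caution to secondary outcomes. A later adjustment would not leave the stated power intact.

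Three stronger readings are tempting, and the article does not support them.
- *That the error rate is 18%.* This needs visit comparisons that do not depend on the interaction. Calling them follow-up analyses may imply that they do, and the same article makes follow-up of its secondary MANOVA conditional on a significant result. No such condition is written for the primary outcomes, so the point is open either way.
- *That the plan breaks a stated 5% overall rate.* The article never states a familywise rate, only a per-test level.
- *That either outcome alone counts as success.* No such rule is written, nor is the opposite one. The Background expects both a bias reduction and a smoking reduction.

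It can also be said that mechanism and behaviour are separate hypotheses, and that the Discussion calls this a proof-of-principle study. Reporting each outcome at its own 5% is defensible if no joint claim is made, but the article would have to say so.

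**Conclusion.** The concern holds in a limited form. Two primary outcomes are each tested at 0.05, with neither a success rule nor error control. The chance of at least one false primary finding is about 10% across the two interaction tests. This assumes that neither outcome responds and that a significant result on either is reported as a primary finding; it changes little for outcome correlations up to 0.5. About 18% applies only if the visit comparisons are run regardless of the interaction. If they are conditional on it, false visit-level claims fall to about 6.5% under the global null. The analyses remain usable. What needs settling is the claim rule and the power that goes with it.

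**What to change.** State one rule with strong control, before any data are seen:

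- **(a)** Test each outcome's condition-by-time interaction at 0.025. Only if it is significant, compare the two visits by Holm at 0.025 within that outcome. Pass no alpha to the other outcome until both visits have also passed.
- **(b)** Apply Holm at 0.05 across the four baseline-adjusted outcome-by-visit comparisons.

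Under either rule, claim success only for the outcomes and visits that pass, and say whether visit comparisons depend on the interaction.

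A tempting shortcut is Holm across the two outcomes, followed by visit tests within each outcome that passes. It does not hold 5%: the second outcome receives the full 0.05 while 0.025 is still being spent on the first outcome's visits. If the first outcome responds at one visit only and the second not at all, the false-claim rate is about 1 − 0.975 × 0.95 = 7.4%; simulation gave 7.4% to 7.7% when an effect exists at one visit only. The even 0.025 split and Holm across the four comparisons stay at about 5%.

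**Cost.** One paragraph of text and a restated power. Under (a), power for each interaction test at f = 0.15 and 74 evaluable is about 72%, against the stated 80%. No extra enrolment is required if the lower power is accepted and stated; restoring 80% would take 118 enrolled. The article gives no separate power figure for the visit comparisons, so (b) would need its own calculation.

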### Sample size

A priori power analyses were conducted using G*Power 3.1 (open-source software [34]). Previous research investigating the effectiveness of CBM training identified a small-to-moderate effect size [21, 35]. We conducted a power analysis for a 2 × 3 mixed design ANOVA to detect a small-to-moderate effect (Cohen’s *d* = 0.30, α = 0.05) for the interaction between experimental condition and time for each primary outcome and time point. Power of 0.80 and *r* = 0.5 for correlation between the repeated measures was assumed. Results indicated that 74 participants in total would be needed. Due to an expected attrition rate of approximately 25% at follow up (defined as dropout at any time point after completing the baseline assessment), we decided to include 100 participants, that is 50 per condition.

We would like to stress that we performed power calculations for primary outcomes exclusively. With regard to secondary outcome measures, we emphasize that the study is explorative, meaning that any significant findings on these outcome variables should be interpreted with caution until tested in further confirmatory RCTs.

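### The 74 participants give about 24–31% power for Cohen's d = 0.30, not the stated 80%, because d/2 was used as the effect size of a 2 × 3 interaction

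*Protocol article*

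**What the plan says.** The Sample size section reads: "We conducted a power analysis for a 2 × 3 mixed design ANOVA to detect a small-to-moderate effect". The inputs are Cohen's d = 0.30, alpha 0.05, power 0.80 and "0.5 for correlation between the repeated measures was assumed". The claim is made "for the interaction between experimental condition and time for each primary outcome and time point". The outcome is: "Results indicated that 74 participants in total would be needed". The total is raised to 100, or 50 per arm: "Due to an expected attrition rate of approximately 25% at follow up".

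Two other sections bear on this. Outcome measures makes both post-training and follow-up primary time points. Data preparation and planned analyses names a 2 × 3 mixed ANOVA for each primary outcome and then says: "Substantive hypotheses will be tested by means of follow-up simple effects analyses". Those analyses compare the arms at post-test and at follow-up, adjusting for baseline.

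**The concern.** Cohen's d is a standardised difference between two means. The power routine for a within-between interaction needs Cohen's f for the interaction, which is the spread of the interaction cell effects relative to the error SD. The rule f = d/2 links the two only for two independent group means. If it was used here, the trial was sized for an effect about twice the one named.

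The per-time-point claim is a second problem. The omnibus interaction test has two numerator degrees of freedom and covers all three visits together, so it says nothing about power at post-test or follow-up separately. The comparisons that carry the substantive hypotheses are not the test used for sizing.

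The Sample size section sets powered primary outcomes against explorative secondary ones. A reader will therefore take the primary results as adequately powered for a small-to-moderate effect, and may read a null result as evidence against d = 0.30.

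**Working it through.** **Inputs (Sample size section):** 2 groups, m = 3 measurements, r = 0.5, alpha = 0.05, target power 0.80, d = 0.30, N = 74 (37 per arm). Assumed, because not stated: two-sided single-visit tests, equal SDs, equal baselines, compound symmetry (sphericity), no multiplicity adjustment.

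**1. Reproducing 74.** For the interaction, λ = f²·N·m/(1 − r), with df 2 and 2(N − 2).

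- f = 0.15, N = 74: λ = 0.0225 × 74 × 3/0.5 = 9.99, df 2 and 144, power 0.806.
- f = 0.15, N = 72: λ = 9.72, power 0.795.

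So 74 is the smallest even total. Other readings fail: f = 0.30 gives 20, two measurements with f = 0.15 give 90, the between-subject main effect gives 236, and alpha 0.025 gives 88.

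**2. What d = 0.30 means for the interaction.** Take group differences of (0, d, d) at baseline, post-test and follow-up.

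- Their mean is 2d/3, so the deviations are (−2d/3, d/3, d/3).
- Half of each falls in each arm with opposite sign, so the cell effects are ±(d/3, d/6, d/6) in absolute size.
- f² = d²(1/9 + 1/36 + 1/36)/3 = d²/18, so f = d/√18 = 0.236d.

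The pattern (0, 0, d) gives the same f. A linear build-up (0, d/2, d) gives f = d/√24.

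- d = 0.30 gives f = 0.30/√18 = 0.0707.
- f = 0.15 gives d = 0.15 × √18 = 0.636.

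**3. Interaction power at d = 0.30.**

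- N = 74: λ = 0.005 × 74 × 6 = 2.22, power 24.2%. A simulation of 20,000 trials gave 24.5%; at d = 0.636 it gave 80.8%.
- N = 74, linear build-up to 0.30: λ = 0.00375 × 74 × 6 = 1.665, power 19.1%.
- N = 100, no loss: λ = 3.00, power 31.7%.
- N for 80% power: 324 (λ = 0.005 × 324 × 6 = 9.72).

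**4. Power at one visit, d = 0.30.** The noncentrality is d/√(2v/n). The variance factor v is 1 unadjusted (or for a change score at r = 0.5) and 1 − r² = 0.75 with baseline adjustment.

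| Comparison | n per arm | Noncentrality | Power |
|---|---|---|---|
| Unadjusted | 37 | 1.29 | 24.7% |
| Baseline-adjusted | 37 | 1.49 | 31.2% |
| Unadjusted | 50 | 1.50 | 31.8% |
| Baseline-adjusted | 50 | 1.73 | 40.3% |

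The adjusted comparison needs 132 per arm (264 in total) for 80% power.

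**5. Effect detectable with 80% power at N = 74.** d is about 0.63 for the interaction, 0.57 for one baseline-adjusted visit and 0.66 unadjusted.

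**6. Sensitivity to r, N = 74.** The documents give no value other than 0.5, so this range is illustrative.

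| r | Interaction, f = 0.15 | Interaction, d = 0.30 | One adjusted visit, d = 0.30 |
|---|---|---|---|
| 0.2 | 59% | 17% | 25% |
| 0.5 | 81% | 24% | 31% |
| 0.7 | 96% | 38% | 43% |
| 0.8 | >99% | 54% | 56% |
| 0.9 | >99% | 85% | 83% |

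**7. Attrition.** 74/0.75 = 98.7, so 99, rounded up to 100. This step is sound.

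**The case against.** The software arithmetic is correct for f = 0.15. If the authors obtained d as 2f from an interaction effect size, then d = 0.30 and f = 0.15 describe the same effect and 74 follows. How the cited studies scaled their effects cannot be checked from the article. But the text says Cohen's d without qualification and attaches it to each time point, which is how a group difference at a visit is described. Even on the rescaled reading, the planning effect is a visit-level difference of about 0.64, which is hard to call small-to-moderate.

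Multiple imputation is planned for the intention-to-treat analysis, so the effective information lies between that of 74 and that of 100 participants. That is fair, and it widens the range to about 24–40%, still far below 80%.

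A higher correlation would help. At r = 0.8 power is 54–56%, and it passes 80% only near r = 0.9. The protocol assumes 0.5, and the approach-bias score is a difference of reaction times, for which high stability should not be presumed.

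Finally, the Discussion calls this a proof-of-principle study and no rule for reading a null result is given, so misreading is a risk rather than a certainty. That tempers the consequence but leaves the stated power wrong.

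**Conclusion.** The concern holds. The stated 80% power for d = 0.30 is not delivered. At the protocol's own r = 0.5, 74 participants give 24% (interaction) to 31% (one baseline-adjusted visit), and full retention of 100 gives 32% to 40%. The design has 80% power only for an effect about twice the one stated. These figures read d as a standardised group difference at a post-baseline visit and rest on the assumptions listed with the inputs. Separately, and on any reading of d, an omnibus interaction calculation cannot support a power claim for each time point.

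**What to change.** Keep 100 participants and rewrite the Sample size section:

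- State that with about 75 completers and r = 0.5 the trial has 80% power for a between-group difference of about d = 0.63 on the interaction, or about 0.57 at one visit after baseline adjustment.
- State that power for d = 0.30 is about 24–31% at that number, and 32–40% if all 100 are retained.
- Delete the per-outcome and per-time-point wording, or base the calculation on the baseline-adjusted comparison that will be used.
- Give the effect size actually entered in the software (f), and show sensitivity to r in both directions, above all for the approach-bias score.

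The cost is rewording and a less favourable stated figure, with no extra participants. If d = 0.30 is to remain the target, about 264 (adjusted visit) to 324 (interaction) analysed participants are needed, or 264/0.75 = 352 to 324/0.75 = 432 recruited at 25% attrition. Trial status says the trial had not started at submission, so the sponsor should make that choice openly.
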